## Abstract

**Background:**

We conducted a prospective randomized study of an adjuvant oxaliplatin-based regimen plus orally administered tegafur-uracil in patients with stage III colon cancer after radical resection to evaluate the feasibility of this drug combination in cancer clinical outcomes, acute toxicity, disease-free survival (DFS), and overall survival (OS) in Taiwan.

**Methods/design:**

This is an open-label, randomized, comparative, double-arm, multicenter, phase III study to assess DFS, OS, and safety profiles of the aforementioned drug combination as maintenance therapy for 1 year in patients with stage III colon cancer after radical resection in Taiwan. Following the completion of an adjuvant oxaliplatin-based regimen for 3 weeks with no evident disease recurrence, all eligible patients will be randomly assigned to either arm A (maintenance therapy) or arm B (observation arm) in a 2:1 ratio (364 and 182 patients in the tegafur-uracil and observation groups, respectively). Treatment in arm A will be started within 7 days of randomization. If the patients reported disease recurrence, intolerable toxicity, withdrew consent or the investigator determined that the patient should be withdrawn during the study period, they were withdrawn from the study. If a patient was discontinued from the study, the corresponding data were not reused, and the patient was not allowed to re-enter the study.

**Discussion:**

A unique characteristic of this intervention was that the adjuvant chemotherapy with oxaliplatin and tegafur-uracil was anticipated to be safe and has high treatment efficacy, with the advantage of yielding a favorable response rate and tolerable toxicity profile.

**Trial registration:**

ClinicalTrials.gov, identifier: NCT02836977. Registered on 18 July 2016.

**Electronic supplementary material:**

The online version of this article (doi:10.1186/s13063-017-1904-9) contains supplementary material, which is available to authorized users.

## Background

### Epidemiology

Colorectal cancer (CRC), the most frequently diagnosed cancer, is the third leading cause of cancer-related deaths in Taiwan. During the past decade, the incidence rate of CRC has increased from 38 to 70 per 100,000 men and 30 to 51 per 100,000 women. The annual incidence of CRC in Taiwan has increased up to 43.5% in the past decade, with more than 15,000 new cases and >5000 deaths annually; among these patients, approximately one fourth had stage III disease according to the Taiwan Cancer Registry Database [1, 2]. Approximately 42% of stage III colon cancer cases have recurrences within 8 years after radical resection. In the 8-year follow-up period, 82% of patients with stage III colon cancer experienced recurrences in the initial 3 years [3].

### Current treatment modality

Intravenously administered (IV) 5-fluorouracil (FU) has been the most widely used chemotherapeutic agent for CRC for more than 40 years [4] and is included in various combination treatments such as those with oxaliplatin and irinotecan with or without biological agents (i.e., cetuximab and bevacizumab) [5]. Since 2004, FOLFOX4 (85 mg/m^2^ oxaliplatin combined with 200 mg/m^2^ leucovorin (LV) over 2 h, followed by a 400-mg/m^2^ 5-FU bolus and 22-h continuous infusion of 600 mg/m^2^ 5-FU) has been the accepted first-line therapy in advanced CRC [6]. The FOLFOX6 regimen comprises 100 mg/m^2^ oxaliplatin and 400 mg/m^2^ LV as a 2-h infusion on day l, followed by a 400-mg/m^2^ 5-FU IV bolus and a 46-h continuous infusion of 2400–3000 mg/m^2^ 5-FU; this regimen was repeated at 2-week intervals.

### Investigational product (IP) description

Tegafur-uracil, containing tegafur and uracil in a molar ratio of 1:4, is an antimalignant tumor agent with an antimetabolic effect. Tegafur is metabolized in vivo to 5-FU, which is a pyrimidine analog antimetabolite that is metabolized to 5-fluoro-2’-deoxyuridine monophosphate (FdUMP) and 5-fluorouridine triphosphate (FUTP). FdUMP inhibits deoxyribonucleic acid (DNA) synthesis by binding to thymidylate synthase and inhibiting thymidylate production. FUTP interferes with ribonucleic acid (RNA) processing when it is mistakenly incorporated instead of uridine triphosphate. Uracil facilitates maintaining intracellular levels of 5-FU by inhibiting its degradation.

Clinical trials have confirmed that the optimal combination ratio of tegafur-uracil yields long-lasting characteristics and high 5-FU concentrations in tumors. They have revealed the efficacy of tegafur-uracil as an antitumor agent for treating head and neck, gastric and breast cancers and CRC.

### Preclinical data

Tegafur-uracil can inhibit the growth of tumors such as Walker 256 carcinosarcoma, Yoshida sarcoma, ascites carcinoma (in rats), sarcoma 180, Ehrlich carcinoma, Lewis lung carcinoma, and B-16 melanoma (in mice) transplanted subcutaneously. It can also inhibit the growth of human cancers, such as gastric, beast, and pancreatic cancers, when transplanted subcutaneously in nude mice. In addition, its survival effects have been proven in animals (mice) bearing L1210 transplanted leukemia.

The antitumor activity of tegafur-uracil is based on 5-FU that appears gradually in the body through the transformation of tegafur. The mechanism of 5-FU is considered to be the inhibition of DNA synthesis, resulting from the antagonistic effect of the active metabolite FdUMP on dUMP to inhibit thymidylate synthase, and RNA-function disorders, resulting from the incorporation of FUTP into RNA. Uracil enhances the antitumor activity of tegafur.

### Clinical data and experience

The efficacy of adjuvant treatment in CRC was clearly demonstrated as recently as the early 1990s, and 5-FU + LV became the standard treatment for stage III colon cancer in 1996 [7, 8]. The MOSAIC trial [9] demonstrated the superiority of FOLFOX4 over 5-FU + LV, and in 2004, the FOLFOX4 regimen became the standard adjuvant treatment for stage III colon cancer.

Several clinical trials have demonstrated the efficacy of tegafur-uracil in postoperative adjuvant chemotherapy. The basic data from these studies indicate a possible contribution of the antiangiogenic activity of tegafur-uracil to its overall antitumor activity, which until now has been considered to be mediated by the cytotoxic effects of 5-FU. Thus, tegafur-uracil seems to be particularly useful in a chronic postoperative adjuvant chemotherapy regimen to prevent cancer progression.

Each cycle of tegafur-uracil + LV reduced the mean clinical visits by 66%, house staff visits by 17%, health professional visits by 36%, transfusion procedures by 74%, and diagnostic procedures by 33% compared with 5-FU + LV. In addition, tegafur-uracil + LV reduced monthly clinical visits of each patient by 4.5 h compared with 5-FU + LV. Tegafur-uracil + LV was associated with lower resource use than was an 5-FU + LV IV bolus, mainly because of fewer hospitalizations for the treatment of adverse events (AEs; tegafur-uracil + LV (21%) versus 5-FU (36%)) [10].

### Trial rationale

Additional maintenance therapy (12 cycles of tegafur-uracil (400 mg daily) + LV ((60 mg daily) for 28 days at a 7-day interval), followed by six cycles of 5-FU (375 mg/m^2^) + LV (30 mg daily) by a rapid IV injection for 5 days every 4 weeks (the Mayo Clinic regimen) significantly enhanced disease-free survival (DFS) compared with 5-FU + LV in patients with stage III colon cancer [11]. In patients with advanced CRC, a sequential therapy with a highly active chemotherapeutic regimen (e.g., FOLFOX4) for 6 months, followed by maintenance therapy with orally administered fluoropyrimidine (e.g., tegafur-uracil) is advantageous for obtaining a favorable toxicity profile and ease of administration by the oral route which is preferable for patients because of the more convenient outpatient therapy. The maintenance therapy with oral tegafur-uracil for patients responding to FOLFOX4 can maintain the treatment response and improve quality of life because it allows an outpatient regimen and the oral therapy entails lower psychological distress [5].

Adjuvant chemotherapy may prolong the 3-year DFS in patients with stage III colon cancer. However, cold-triggered, acute sensory reversible neuropathy and treatment-limiting chronic sensory neurotoxicity are associated with the cumulative dose of oxaliplatin [12], which is an indication to stop oxaliplatin treatment in patients who are still responding to treatment. Therefore, we designed a trial to demonstrate the utility of maintenance therapy with tegafur-uracil in patients with stage III colon cancer after a 6-month oxaliplatin-based regimen. The primary objective of this trial was to verify the 3-year DFS after 1 year of tegafur-uracil treatment.

## Objective

### Primary objective

To compare the 3-year DFS of tegafur-uracil following an adjuvant oxaliplatin-based regimen with that of an adjuvant oxaliplatin-based regimen in patients with stage III colon cancer after radical resection.

### Secondary objectives

To assess and compare the 5-year overall survival (OS) in maintenance therapy and observation armsTo assess and compare the safety profiles in both arms

## Patient selection and enrollment

### Patient number

Eligible patients will be randomized in two arms in a ratio of 2:1 to reach an approximate total of 546 patients. The sample size ratio is 2:1 (study arm is 2, control is 1), treatment duration is 1 year. Based on data of the 3-year DFS rate from our previous retrospective study, the proportion of control arm is 0.55 (55%) and of the study arm is 0.7 (70%) with a significance level of 0.05 and a power of 80%.

### Inclusion criteria

For inclusion in the study, each patient must fulfill the following criteria:Pathology-confirmed colon carcinomaStage III disease (T_1–4_, N_1–2_, and M_0_, as defined by the American Joint Committee on Cancer (AJCC) 7th edition)Completion of an adjuvant oxaliplatin-based regimen, with no evident disease recurrenceEntry in the trial within 3 weeks of an adjuvant oxaliplatin-based regimenEastern Cooperative Oncology Group (ECOG) status of 0–2Aged 20–80 yearsWritten informed consent provided to participate in the trial

### Exclusion criteria

Patients fulfilling any of the following criteria will be excluded from the trial:Previous or current systemic malignancy except curatively treated nonmelanoma skin cancer or in situ cervical carcinoma, unless there exists a DFS of at least 5 yearsInadequate hematopoietic function defined as follows:Hemoglobin < 9 g/dLAbsolute neutrophil count (ANC) < 1500/mm^3^
Platelet count < 100,000/mm^3^

Inadequate organ functions defined as follows:Total bilirubin >2 times the upper limit of normal (ULN)Hepatic transaminases (alanine aminotransferase (ALT) and aspartate aminotransferase (AST)) >2.5 × ULNCreatinine >1.5 × ULN
Other severe medical conditions that are contraindicated to tegafur-uracil or render patients at a high risk of treatment complications based on investigator discretionPresence of other severe concomitant illnessParticipation in another clinical trial with any investigational product (IP) within 30 days before study entryPregnant or lactating women or women of childbearing potential

### Trial enrollment method (Fig. 1,  Fig. 2)

**Fig. 1 Fig1:**
[figure not shown]
Trial enrollment. Stage III disease: T_1–4_, N_1–2_, and M_0_, as defined by the AJCC 7th edition. Completion of an adjuvant oxaliplatin-based regimen with no evident disease recurrence. The patients were withdrawn in cases of disease recurrence, intolerable toxicity, or consent withdrawal during the study

**Fig. 2 Fig2:**
[figure not shown]
Flowsheet for pre/post-treatment investigations

Patient eligibility criteria will be established before treatment enrollment.

Following the completion of an adjuvant oxaliplatin-based regimen within 3 weeks with no evident disease recurrence, all eligible patients will be randomly assigned to either arm A (maintenance therapy) or arm B (observation arm) in a 2:1 ratio (364 and 182 patients in the tegafur-uracil and observation groups, respectively). Treatment in arm A will be started within 7 days of the randomization.

If the patients report disease recurrence, intolerable toxicity, or consent withdrawal or are removed according to the investigator’s discretion during the study period, they will be withdrawn from the study. If a patient wishes to discontinue the study, the corresponding data will not be reused, and the patient will not be allowed to re-enter the study.

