### Treatment duration

Treatment will be administered for up to a maximum of 1 year, and in case of disease progression, intolerable toxicity, or consent withdrawal during the study, the patients will be withdrawn.

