### Dose modification

The dose after the first treatment will be modified on the basis of the highest toxicity degree graded according to National Cancer Institute Common Terminology Criteria for Adverse Events (NCI-CTCAE) v4.03For toxicities that are considered by the investigator to be unlikely to become severe or life-threatening and that do not result in a delay or interruption of therapy (e.g., alopecia and altered taste), treatment will be continued at the same dosing without reduction or interruption. No dose reductions or interruptions are required for anemia because it can be satisfactorily controlled by transfusionsFor the patients experiencing treatment interruption because of AEs for more than 2 weeks, treatment discontinuation will be considered (Table 2)

**Table 2 Tab2:** Dose modification

Toxicity (grade)	Dose modification
ANC <1000/mm^3^	Discontinue the treatment until ANC ≥1500/mm^3^; resume the treatment with the same dose
Platelets <50,000/mm^3^	Discontinue the treatment until platelets ≥100,000/mm^3^; resume the treatment with the same dose
Other toxicities	No dose modification or interruption required
Grades 1 and 2	Discontinue the treatment until returns to baseline; resume the treatment to 200 mg daily
Grades 3 and 4	
*ANC* absolute neutrophil countDiscontinuation of study participation

If the patients experience any of the following consequence during the study, they will be withdrawn from the study treatment:Disease recurrenceIntolerable toxicityConsent withdrawalInvestigator discretion

All information regarding the withdrawal will be recorded in the Case Report Form (CRF)

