Statistical analysesDemographic and baseline measuresAll demographic and baseline data will be summarized and listed in detail. For continuous variables, the descriptive statistics, including the patient number, mean, median, standard deviation, and range (minimum-maximum) will be presented; frequency tables will be displayed for categorical data. If demographic and baseline measures are significant, their inclusion in the analysis model will be consideredThree-year disease-free survival (DFS)Three-year DFS will be defined as the percentage of patients alive without disease recurrence at 3 years measured from the randomization date. The 3-year DFS will be evaluated using the Kaplan-Meier method, and the analysis will be presented in descriptive statistics, presented by a point estimate and 95% confidence interval. The results will be summarized in the form of the sample size, mean, standard error, median, percentiles, and range by descriptive statistical methodsFive-year overall survival (OS)Five-year OS will be defined as the percentage of patients alive at 5 years measured from the randomization date. The 5-year OS will be evaluated using the Kaplan-Meier method, and the analysis will be presented in descriptive statistics, presented by a point estimate and 95% confidence interval. The results will be summarized in the form of the sample size, mean, standard error, median, percentiles, and range by using descriptive statistical methodsSafety profileAEs will be summarized using NCI-CTCAE v4.03 and the preferred term. The incidence and percentage of patients with at least one occurrence of a preferred term will be included according to the most severe NCI-CTCAE v4.03 grade. Laboratorial toxicity will be presented according to the highest NCI-CTCAE v4.03 grade by cycle

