### Trial status

The trial started in July 2016 and is expected to enroll 546 patients in the study and control groups by the end of July 2018.

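### The protocol contradicts itself on whether recurrence or toxicity ends study treatment or study participation, and its minimum duration is not tied to the last patient, so 5-year overall survival is not secured

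*Protocol article*

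**What the plan says.** **Withdrawal.** Several places in the protocol article describe what happens at recurrence, intolerable toxicity or consent withdrawal. Three of them (the abstract, Trial enrollment method and Dose modification) add investigator discretion.

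- Trial enrollment method: such patients leave the study: "during the study period, they will be withdrawn from the study". The abstract (Methods/design) says the same.
- Dose modification, in the list on discontinuing study participation: "they will be withdrawn from the study treatment".
- Fig. 1 legend: "The patients were withdrawn in cases of disease recurrence, intolerable toxicity, or consent withdrawal during the study". It does not say from what.
- Treatment duration: "in case of disease progression, intolerable toxicity, or consent withdrawal during the study, the patients will be withdrawn". Again no object is given.

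Trial enrollment method adds, for a patient who wishes to discontinue, that "the corresponding data will not be reused, and the patient will not be allowed to re-enter the study". The abstract applies similar wording to any discontinued patient.

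**Endpoints.** The Efficacy measurements section measures OS from randomisation to death and calls 3-year DFS and 5-year OS primary; the Objective section lists 5-year OS as secondary. The statistical section states: "Five-year OS will be defined as the percentage of patients alive at 5 years measured from the randomization date", estimated by Kaplan-Meier.

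**Follow-up and calendar.** Table 3 plans CEA and abdominal echo in the 3rd to 5th years but has no survival-status row. After early treatment stop, the only follow-up stated is for serious adverse events, in the main until 30 days after the last dose or the start of another antitumour therapy. Study schedule gives 24 patients per month, at least 2 years of recruitment and a duration of at least 5 years. Trial status says the trial, begun in July 2016, "is expected to enroll 546 patients in the study and control groups by the end of July 2018".

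**The concern.** A site reading the enrolment section would close a patient's record at recurrence. A site reading the dose-modification section would stop the drug and keep following the patient. For OS these are different trials. In stage III colon cancer most deaths from the disease come after recurrence, so the first reading removes patients from the risk set just when their risk of death rises. That censoring is informative, and no later analysis choice repairs it if the deaths were never recorded.

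For DFS the exposure is narrower. A patient withdrawn for toxicity or at the investigator's discretion before recurrence would be censored early, and study-drug toxicity can arise only in arm A because arm B is observed.

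The calendar is a second, independent weakness. A 5-year minimum that is not counted from the last randomisation does not guarantee 5 years of follow-up for a 5-year endpoint.

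**Working it through.** **1. The texts side by side.** Only the abstract and Trial enrollment method carry the wording that ends study participation. Dose modification carries the wording that ends treatment. The Fig. 1 legend and Treatment duration fit either reading; the latter stands in a sentence about how long treatment is given and reads more naturally as treatment only. So two places conflict with one, and two are ambiguous.

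**2. How many patients are affected.** Inputs from Patient number: 3-year DFS 0.55 (control, n = 182) and 0.70 (study, n = 364).

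- Control: 0.45 × 182 = 81.9 DFS events by year 3.
- Study: 0.30 × 364 = 109.2.
- Total 191.1, which is 35% of 546.

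This is an upper figure for exits at recurrence, because the statistical section's DFS also counts death without recurrence.

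**3. What Kaplan-Meier OS would show if follow-up ended at recurrence.** Only deaths without prior recurrence remain. If other-cause mortality is m per year and independent of recurrence, the 5-year estimate is exp(−5m) in both arms, whatever the recurrence pattern.

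- m = 0.01 (assumed): exp(−0.05) = 0.951.
- m = 0.02 (assumed): exp(−0.10) = 0.905.

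**4. What it would miss (illustration).** Let λ be the recurrence hazard and μ the death hazard after recurrence. With λ constant,

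OS(5) = exp(−5m) × [μ·exp(−5λ) − λ·exp(−5μ)] / (μ − λ).

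The planned rates give λ = −ln(0.55)/3 = 0.1993 (control) and −ln(0.70)/3 = 0.1189 (study). An assumed median survival after recurrence of 2 years gives μ = ln 2/2 = 0.3466. With m = 0.01:

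- Control: 0.6296 × 0.9512 = 0.599.
- Study: 0.7477 × 0.9512 = 0.711.

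Over medians of 1.5 to 3 years and m of 1–2%, control runs from 0.52 to 0.67 and study from 0.64 to 0.76, a difference of 8 to 13 points.

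A constant hazard implies 1 − 0.55^(5/3) = 63% recurrence in controls by year 5. That sits badly with the Background section, which reports about 42% recurrence over 8 years after resection, 82% of it in the first 3 years. As a check, I put all recurrences before year 3 and none after. Cancer deaths by year 5 are then

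(1 − S₃) − λ·exp(−5μ)·[exp(3(μ − λ)) − 1]/(μ − λ), with S₃ the planned 3-year DFS.

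With the 2-year median and m = 0.01, OS is (1 − 0.3171) × 0.9512 = 0.650 in control and (1 − 0.2095) × 0.9512 = 0.752 in study. The gap is still about 10 points, against zero in step 3.

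**5. DFS.** Withdrawal at recurrence coincides with the event and adds no censoring. For withdrawal before recurrence, a simulation assumed that 5–20% of arm A leave for toxicity during year 1, with a later recurrence hazard 1 to 2 times that of the others.

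| Left for toxicity | Later hazard ratio | True 3-year DFS | Kaplan-Meier |
|---|---|---|---|
| 20% | 1 | 0.698 | 0.699 |
| 10% | 1.5 | 0.690 | 0.700 |
| 20% | 2 | 0.665 | 0.701 |

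The bias runs from nil to about 3.6 points in favour of arm A.

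**6. Calendar.** Accrual is 546/24 = 22.75 months, in line with July 2016 to July 2018 (about 24 months).

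- Close at 60 months: the last patient has 60 − 22.75 = 37.25 months (36 with 24-month accrual). All reach 3 years; essentially none has a full 5.
- Close at 66 months, uniform accrual: 546 × 6/22.75 = 144 patients have 5 years of potential follow-up.
- Close at 72 months: 546 × 12/22.75 = 288.
- All 546: 22.75 + 60 = 82.75 months (84 with 24-month accrual).

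**The case against.** The strongest reply is that the benign reading is available. Dose modification speaks of treatment only, and Treatment duration fits it. Table 3 foresees assessments in years 3 to 5, so about five years per patient is evidently intended, and at least 5 years fixes no closing date. A condensed article need not describe survival contacts in detail. All of this stands, and it rules out the stronger inference that 5-year OS cannot be observed. It does not remove the contradiction: the enrolment section and the abstract still tell sites to end participation.

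Some other readings also go too far.

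- A reader might infer that DFS is informatively censored by withdrawal at recurrence. It is not, because recurrence is the DFS event; only earlier withdrawals matter.
- A reader might infer that data already collected are discarded from everyone who leaves. In Trial enrollment method the sentence "the corresponding data will not be reused" concerns patients who wish to discontinue. The abstract is broader, but neither says that collected data leave the analysis, and the per-protocol definition keeps confirmed early recurrences.
- A reader might treat closure at 60 months as a further bias. It would be administrative, non-informative censoring. The log-rank test stays valid; what suffers is the 5-year Kaplan-Meier estimate.

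The OS sizes are also open to attack. Post-recurrence survival and other-cause mortality are not in the documents. The model also assigns every planned DFS event to recurrence and then adds other deaths, so its DFS falls slightly below the planned 55% and 70%. The direction of the bias survives this; the exact size does not.

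**Conclusion.** The point holds as an unreconciled contradiction plus a study end that is not anchored to the last patient. If the enrolment wording is followed, OS is informatively censored at recurrence, overstated in both arms, and loses most of its contrast. Under assumed other-cause mortality of 1–2% per year it would read about 90–95% in each arm, where the illustrative true values differ by roughly 8 to 13 points. Those figures show scale only.

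For DFS the possible bias is limited to withdrawals before recurrence for toxicity or at investigator discretion, and is probably modest: 0 to about 3.6 points under the assumed rates. Three-year DFS is reachable even if the study closes at its minimum. Five-year OS is not secured at that minimum, because the last patient would have only about 3 years. Because the protocol itself calls 5-year OS primary in one section, and follow-up not collected after recurrence may not be fully recoverable, this needs correcting.

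**What to change.** Reconcile the abstract and Trial enrollment method with Dose modification, so that stopping study treatment is distinct from leaving the study, and say in the Fig. 1 legend and Treatment duration which of the two is meant. Then state:

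- In both arms, follow-up for recurrence continues after treatment stops, and follow-up for survival continues after recurrence, for 5 years from each patient's randomisation.
- Only withdrawal of consent to follow-up ends data collection, and data up to that date stay in the analysis.
- The study ends 5 years after the last randomisation, about 7 years after the first.

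Add a survival-status row to Table 3. Five years per patient is enough for the endpoint; early recruits need no longer schedule.

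The cost is survival-status contacts after recurrence or treatment stop, and about two calendar years beyond the stated minimum. No treatment-stopping rule changes.

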#### Statistical methods and sample size determination

This is an open-label, randomized, comparative, double-arm, multicenter, phase III study of tegafur-uracil following an adjuvant oxaliplatin-based regimen in patients with stage III colon cancer after radical resection.Statistical evaluationStatistical analysis methodsA comprehensive statistical analysis plan will be prepared before database lock. The patients will be categorized into the Full Analysis Set (FAS), per protocol (PP), and safety populations according to the following definitions:Full Analysis Set (FAS):The FAS is defined as containing all registered and randomized patients who received at least one dose of the study treatment without major protocol violations, such as noncompliance with the eligibility criteria, or other major violations (defined before database lock) during the studyIntent-to-treat (ITT):The ITT population is the subset of the FAS population, and as all randomized patients irrespective of treatment receivedPer protocol (PP):The PP population is the subset of the ITT population and subjects who complete 12 months of tegafur-uracil treatment/observation with at least one biomarker assessment post treatment. The subject with confirmed early disease recurrence/relapse would be included in the PP population. The patients with confirmed early disease recurrence and relapse will be included in the PP population.All the efficacy endpoints will be analyzed in the FAS and PP populations. The main assessment will be performed on the basis of the PP population.The safety population is defined as all patients who are exposed to at least one dose of the study treatment and who are available for obtaining follow-up safety information

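### The clause that a discontinued patient's data are not reused has two different scopes, conflicts with the analysis sets, and read plainly drops outcomes already collected from patients who choose to leave

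*Protocol article*

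**What the plan says.** The protocol article states the rule twice.

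- **Abstract, Methods/design.** After naming recurrence, intolerable toxicity, consent withdrawal and investigator decision as reasons for withdrawal, it says: "If a patient was discontinued from the study, the corresponding data were not reused". No reason is exempted.
- **Trial enrollment method.** The same four reasons lead to withdrawal from the study ("If the patients report disease recurrence, intolerable toxicity, or consent withdrawal or are removed" opens that sentence). The data rule itself is narrower. It applies only where the patient wishes to stop, in which case "the corresponding data will not be reused, and the patient will not be allowed to re-enter the study".

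Two other sections bear on it.

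- **Dose modification, discontinuation of study participation.** For the same reasons, patients are taken off treatment only: "they will be withdrawn from the study treatment". Details of the withdrawal go into the case report form.
- **Statistical methods and sample size determination.** The intent-to-treat set is all randomized patients. The safety set is all patients with at least one dose and available safety follow-up. On recurrence it says: "The patients with confirmed early disease recurrence and relapse will be included in the PP population". Efficacy is analysed in FAS and PP, and "The main assessment will be performed on the basis of the PP population".

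**The concern.** The point concerns data gathered before a patient leaves, not follow-up afterwards. The usual handling keeps everything observed up to departure and censors time-to-event outcomes there. A rule that such data are not used, if applied as worded, removes the patient from the analysis instead.

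Leaving is plausibly related to arm. The trial is open-label, and arm A takes capsules twice daily for a year while arm B is observed. If those who leave are doing worse than those who stay, removing them flatters the arm with more leavers. It also loses adverse events that were recorded before they left.

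The two statements of the rule cover different patients, and no section says which governs. A site or data manager therefore has no single instruction to follow.

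**Working it through.** **Step 1: whom the clause reaches, by reason for leaving**

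| Reason | Abstract | Trial enrollment method | Statistical methods |
|---|---|---|---|
| Recurrence | data not reused | not covered by the data rule | confirmed early recurrence kept in PP |
| Toxicity, investigator decision | data not reused | not covered by the data rule | no exclusion of collected data stated; PP needs 12 months completed |
| Patient's wish | data not reused | data not reused | as above |

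Loss of recurrence events therefore follows only from the abstract, and the PP definition contradicts it. Patients who choose to leave are the one group caught by both statements.

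**Step 2: which analyses change for patients who choose to leave**

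- *PP, leaving in year 1 without recurrence:* already outside PP, which requires 12 months of treatment or observation. The clause adds nothing here.
- *PP, leaving after 12 months:* they qualify for PP, and Table 3 plans follow-up to year 5. The clause would drop their observed time and events.
- *FAS:* its definition does not require 12 months, so leavers at any time are affected.
- *Safety set:* adverse events recorded before departure are affected.

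**Step 3: possible size**

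The document gives no leaving rate and no figure for the effect of this clause, so there is nothing of its own to reproduce.

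Inputs from the document: 3-year DFS of 70% (arm A) and 55% (arm B) under Patient number; 364 and 182 patients.

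Assumed inputs: leaving fraction *f* of 10-20% in arm A and 2-5% in arm B; leavers' 3-year DFS *d* 10-20 points below their arm's.

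Patients removed:
- arm A: 364 × 0.10 = 36 to 364 × 0.20 = 73
- arm B: 182 × 0.02 = 4 to 182 × 0.05 = 9

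DFS among those retained = (arm DFS − *f* × *d*) / (1 − *f*).

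| Arm | *f* | *d* | Retained DFS | Shift, points |
|---|---|---|---|---|
| A | 0.10 | 0.60 | (0.70 − 0.060)/0.90 = 0.711 | +1.1 |
| A | 0.15 | 0.55 | (0.70 − 0.0825)/0.85 = 0.726 | +2.6 |
| A | 0.20 | 0.50 | (0.70 − 0.100)/0.80 = 0.750 | +5.0 |
| B | 0.02 | 0.45 | (0.55 − 0.009)/0.98 = 0.552 | +0.2 |
| B | 0.05 | 0.35 | (0.55 − 0.0175)/0.95 = 0.561 | +1.1 |

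Between-arm overstatement:
- low case: 1.1 − 0.2 = 0.9 points
- high case: 5.0 − 1.1 = about 4 points

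These pair low with low and high with high. Crossing the leaving rates at a common deficit widens the range:
- *f* of 10% and 5%, deficit 10 points: 1.1 − 0.5 = 0.6
- *f* of 20% and 2%, deficit 20 points: 5.0 − 0.4 = 4.6

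The benchmark is full follow-up of every randomized patient. Keeping data to departure and censoring there would recover only part of this shift if leaving is related to prognosis. Compared with a censored analysis, dropping the time of patients who left disease-free can even lower an arm's estimate. The calculation therefore shows the order of size and does not forecast the bias.

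**The case against.** The strongest reply is that the clause never says data are excluded or left unanalysed. In full it reads "the corresponding data will not be reused, and the patient will not be allowed to re-enter the study". Joined to the bar on re-entry, it may mean only that earlier data are not used again if the patient returns. That reading is possible and keeps this point from being a settled deletion. It does not remove the problem. The text speaks of data, re-entry already has its own clause, and exclusion is a reasonable reading for someone applying it.

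A reader might infer that every DFS event is deleted, because recurrence is a withdrawal reason. The documents do not support that. The enrolment section ties the data rule to the patient's wish, the PP definition keeps confirmed early recurrences, and 3-year DFS is defined as the percentage alive without recurrence, so recurrences must count.

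It may also be said that other sections protect safety data: Reporting requires all adverse events to be recorded, and Follow-up pursues unresolved serious events after participation ends. Both govern collection. Neither says that the events of a discontinued patient enter the analysis.

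Two limits stand. Most of the arm-related leaving argument concerns year 1, and for patients without recurrence the PP definition already excludes them from the main analysis. Arm B patients can also leave the study, so a shift computed for arm A alone would overstate the bias. The intent-to-treat set gives little protection, since efficacy is analysed in FAS and PP.

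**Conclusion.** The point holds as an unreconciled contradiction between the abstract, the enrolment section, the discontinuation text and the analysis sets. It should be corrected, but it does not undermine the trial.

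The firm part is textual: one rule with two scopes, whose plain reading discards observed outcomes that the analysis-set definitions would keep. The exposure lies in FAS, the safety set and PP patients who leave after month 12.

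On the assumed leaving rates and prognosis, the overstatement is about 1-4 points of a planned 70 − 55 = 15. That rests wholly on assumptions and on the clause being applied as exclusion. It describes a set that drops leavers at any time, such as FAS. In PP only the later leavers count.

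A related conflict is that recurrence takes a patient out of the study in two places and off study treatment in a third. If the first is followed, follow-up for 5-year overall survival could end at recurrence.

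**What to change.** Replace the clause in the abstract and in Trial enrollment method with: *The patient may not re-enter or be re-randomized. All data collected up to discontinuation or consent withdrawal, including recurrence, death and adverse events, are retained and analysed in the randomized arm.* Apply it to every reason for discontinuation.

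Reconcile withdrawal from the study (abstract and enrolment section) with withdrawal from study treatment (discontinuation text), so that follow-up for 5-year overall survival does not end at recurrence. This concerns data collection only and takes no position on when treatment should stop.

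The cost is a wording change in two places, one reconciliation, and a check that the consent form allows data already collected to be kept. The retention wording needs no extra patients or visits. It should be settled before any data are excluded under the present clause.
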